# SUMMARY

**Rationale:** Fibrin Sealant is known to have some potential benefits for intraoperative use, especially in the acceleration of the coagulation cascade. Most studies with fibrin glue are focussing on the reduction of allogeneic blood transfusion and the possibilities to reduce costs. Firstly, fibrin sealant was made from patients’ blood plasma but the logistic problems made introduction in general hard. Now Sanquin has produced a CryoSeal (fibrin sealant) made of single-donor plasma which can be used during surgery. This application is already used in cardiothoracic surgery.

**Objective:** Is the application of CryoSeal (CS) in primary total knee replacement surgery beneficial for the patient with respect to a faster track and improved postoperative rehabilitation. The beneficial effect may be due to quicker functional knee rehabilitation, by pain reduction, better mobilisation and improved quality of life during the early postoperative period.

**Study design:** Multicenter, randomised controlled trial stratified by clinic.

**Study population:** Patients aged above 18 years scheduled for primary total knee replacement (TKA) because of osteoarthritis or rheumatic arthritis, meeting all the inclusion criteria and none of the exclusion criteria, are eligible for inclusion in the study.

**Intervention:** The intervention is the application of CryoSeal during surgery according to the standardised manner. The control group will receive standard care.

**Main study parameters/endpoints:** Primary endpoint: Difference in extension knee function 2 and 6 weeks after surgery. Secondary endpoints: postoperative complications, Pain score, knee function Flexion/Extension, Barthel score (day 3); Outpatient department scores (2 weeks, 6 weeks and 3 months, 1 year): Complications, Pain knee function, KSS, KOOS, SF-12, IPQ-K and EQ5D. A pre- and postoperative hand strength measurement will be performed since this might be a predictor of outcome after TKA. (Taekema 2010). Where possible, an actual physical activity measurement will take place to objectively analyse pre- and post operative acitivity level. (Groot, de 2008)

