**Outpatient department (2 weeks, 6 weeks and 1 year)**

- Complications (all timepoints)
- Pain score (all timepoints)
- Knee function F/E (all timepoints)
- KSS (6 wks, 1 year)
- Oxford Knee Score (OKS) (2, 6 wks, 1 year)
- Barthel index (2, 6 wks and 1 year)
- KOOS (6 wks and 1 year)
- SF-12 (6 wks and 1 year)
- IPQ-K (6 wks and 1 year)
- EQ5D (2, 6 wks and 1 year)

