**6.3 Study procedures**

| **Evaluation** | **Pre-op** | **OR (day 0)** | **Postoperative** | | | | | | |
| --- | --- | --- | --- | --- | --- | --- | --- | --- | --- |
| **Day 1** | **Day 2** | **Day 3** | **Discharge** | **2 wks** | **6 wks** | **1 year** |
| **Medical History** |  |  |  |  |  |  |  |  |  |
| **Operation details** |  |  |  |  |  |  |  |  |  |
| **Clinical data** |  |  |  |  |  |  |  |  |  |
| **Laboratory assessment** |  |  |  |  |  |  |  |  |  |
| **Complications** |  |  |  |  |  |  |  |  |  |
| **Pain score** |  |  |  |  |  |  |  |  |  |
| **Function (F/E)** |  |  |  |  |  |  |  |  |  |
| **Barthel score** |  |  |  |  |  |  |  |  |  |
| **KSS** |  |  |  |  |  |  |  |  |  |
| **KOOS** |  |  |  |  |  |  |  |  |  |
| **SF-12** |  |  |  |  |  |  |  |  |  |
| **Oxford Knee Score** |  |  |  |  |  |  |  |  |  |
| **IPQ-K** |  |  |  |  |  |  |  |  |  |
| **EQ5D** |  |  |  |  |  |  |  |  |  |

Table 1; parameters and time points of measuring

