## 10.4 End of study report

The investigator will notify the accredited METC at the end of the study. The end of the study is defined as the last patient’s last visit.

In case the study is ended prematurely, the investigator will also notify the accredited METC, including the reasons for the premature termination.

Within one year after the end of the study, the investigator will submit a final study report with the results of the study, including any publications/abstracts of the study, to the accredited METC.

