1. Hospital stay in days
2. Years of age

Categorized variables

1. Hospital stay: <3; 3-5; 6-8; >8 days
2. Age: >70; 70-60; <60 years of age

The subgroup analyses above are explorative for hypotheses screening.

Extra secondary analyses: Observational analyses of the RCT dataset:

When no correlation between the use of CryoSeal and the pre-, peri- and postoperative variables can be demonstrated and the above estimates are homogenous over the study arms, they will be pooled over the strata before further subgroup analysis; univariate followed by subsequent multivariate analysis will be performed.

The following research questions will be investigated by post-hoc analyses:

Preoperative variables:

1. Is there a correlation between preoperative hand grip strength and postoperative complications after > 1 year?
2. Are there associations between pre-op outcomes of the questionnaires and post-op functional/QoL/complications?
3. Is there a correlation between Range of Motion (ROM) and Oxford Knee Score outcomes?
4. Is there a correlation between preoperative NSAID (incl. Asperin) use and primary and secondary outcomes?
5. Is there a correlation between preoperative Prednison use and primary and secondary outcomes?

Perioperative variables:

1. Is there difference in post-op outcomes between LPS cemented vs cementless (Haga vs Spaarne) knee protheses
2. Is there difference in post-op outcomes (incl. hospital stay, body temp. (if applicable)) or -complications (incl. transfusion reactions) in transfused and non-transfused patients, or patients transfused at different indications/-triggers, and using different type of transfusion products
3. Are there more transfusion reactions in women?
4. Is there a difference in primary and secondary outcome between surgery type (“onder bloedleegte” or not)
5. Is there a difference in mean hospital stay and EPO use (if applicable)
6. Is there a correlation between wound catheter (incl. autologous reinfusion, if applicable) use vs no use and postoperative complications (bleeding, body temp).
7. Is there a correlation between perioperative wound drain reinfusion vs no reinfusion (if applicable) and postoperative complications
8. Is there a correlation between surgery time and postoperative outcomes of the questionnaires
9. Blood losses associated with type of catheter used
10. Is there a correlation between perioperative transfusion trigger (anaemia), age and length of hospital stay

Postoperative variables:

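### The grip-strength question counts complications later than 1 year, but all scheduled follow-up ends at 1 year, so the stated window contains no scheduled complication assessment.

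*Combined protocol and SAP*

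**What the plan says.** The addendum's section on extra secondary, observational analyses lists research questions to be examined post hoc. Question 1 under the preoperative variables is: "Is there a correlation between preoperative hand grip strength and postoperative complications after > 1 year".

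Follow-up is described in four places:

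- **Section 3, flow chart.** The outpatient block is headed "Outpatient department (2 weeks, 6 weeks and 1 year", and its first item is "Complications (all timepoints". Complications are also listed under hospitalisation.
- **Summary.** It adds a visit but has the same end point: "Outpatient department scores (2 weeks, 6 weeks and 3 months, 1 year): Complications, Pain knee function".
- **Section 6.3, Table 1.** The postoperative columns run "Day 1 | Day 2 | Day 3 | Discharge | 2 wks | 6 wks | 1 year".
- **Addendum, outcome lists.** These cover the hospital stay, two weeks, 6 weeks and 1 year, and nothing later.

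Section 10.4 adds: "The end of the study is defined as the last patient’s last visit". The Summary's reason for measuring hand strength is that "this might be a predictor of outcome after TKA".

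**The concern.** The greater-than sign makes 1 year the lower bound of the outcome window, whereas in every schedule 1 year is the upper bound of follow-up. The analysis would look for complications where no visit is planned. It would pass over those recorded in hospital, at 2 and 6 weeks, and at a 1-year visit held on time. A wound infection in week 3 or a re-admission in month 8 would not count.

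This is the only question in the addendum that names preoperative grip strength as a predictor, so it is where the Summary's stated reason for the measurement would be tested. If the window stays as it is, either the analysis rests on a sparse and haphazard set of late reports, or the analyst chooses another window after seeing the data.

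**Working it through.** The plan gives no event count, sample size or power for this question, so there is no figure to reproduce. The check is a count of scheduled complication assessments inside the window under each reading of the wording.

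**Inputs.** Scheduled outpatient assessments are at 2 weeks, 6 weeks and 1 year (flow chart, Table 1), with 3 months added in the Summary. The hospital stay comes before them. For Table 1 I rely on the column headings only.

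| Reading of the window | Hospital stay | Scheduled outpatient assessments inside |
| --- | --- | --- |
| Later than 1 year (literal) | out | 0 |
| At the 1-year visit | out | 1 |
| From surgery up to and including 1 year | in | 3 (4 with the 3-month visit) |

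The literal count of 0 needs no assumption beyond visits held on time. The documents give no visit window, so a 1-year visit held late could fall just past the boundary.

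**Unscheduled time past 1 year.** Section 7.2 records adverse events that patients volunteer or staff notice, and states no cut-off for the individual patient. Section 10.4 ends the study with the last patient, so earlier patients remain within the trial's calendar after their own 1-year visit. The accrual period is not in the documents. Assume uniform accrual over *A* years. The mean time from a patient's 1-year point to the last patient's 1-year visit is then *A*/2:

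- *A* = 1: 0.5 years
- *A* = 2: 1.0 year
- *A* = 3: 1.5 years

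This calendar time is not negligible, but no complication assessment is scheduled in it, and its length depends on the date of enrolment. Section 7.3 keeps open events under follow-up until they resolve or stabilise. That concerns existing events, not new ones.

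**Which data set.** The addendum says only that the database closes later than six weeks after the final operation. At the earliest possible closure, the share of patients past 1 year is (*A* + 6/52 − 1)/*A*:

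- *A* = 1: 0.115/1 = 12%
- *A* = 2: 1.115/2 = 56%
- *A* = 3: 2.115/3 = 71%

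So even a corrected window needs a data set that contains the completed 1-year visits. These shares rest on the accrual assumption and on closure at the lower bound, which the addendum permits but does not state as its intention.

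**The case against.** The strongest reply is that this is loose drafting. The addendum uses the word *after* elsewhere simply to name visit time points, so the phrase may mean complications at the 1-year visit, or over the first year. That is quite possible. But those two readings give different outcomes, as the table shows, and the text chooses neither. The addendum's outcome list names its visits without a greater-than sign, so the sign here is not just house style. Nor do the documents exclude a real interest in late complications. A reader might infer that the authors clearly meant follow-up to 1 year; the text does not establish that.

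A second reply is that the window is not empty. This stands in part. A reader might infer that observation stops altogether at the 1-year visit, but sections 7.2 and 10.4 leave room for later reports. *No scheduled observation* is the accurate description. For the same reason, no percentage of follow-up time lost can be given: it would need a distribution of visit dates and an assumption that recording stops at the visit, and the documents supply neither.

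A third reply is that little hangs on it. This also stands. The question is labelled post-hoc. Complications remain a secondary endpoint and appear in other addendum questions, for instance the second preoperative question, so they are lost to this question only.

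**Conclusion.** The mismatch between window and schedule holds under every objection. As written, the question draws on 0 scheduled complication assessments and leaves out all of those the trial makes: the hospital stay and 3 outpatient visits, or 4 with the Summary's 3-month visit. What could fall inside is passive and unsystematic, so the question cannot be answered reliably.

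A reader might go further and infer that the analysis is bound to report no association. That does not follow. Very few events would make the association inestimable or very imprecise, and the analyst would notice.

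The importance is minor. One exploratory question is affected; the primary endpoint and the comparison between arms are not. The count assumes that 1-year visits are held on time. The calendar-time and data-set figures further assume uniform accrual of 1 to 3 years.

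**What to change.** In preoperative question 1 of the addendum, replace the window with one that the scheduled data support, such as *postoperative complications from surgery up to and including the 1-year visit*. State that the analysis is run on a data set containing the completed 1-year visits. If complications beyond 1 year were truly intended, say that the trial does not collect them systematically and drop the question.

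The cost is one line in the addendum, made before the database is unblinded. It needs no new data or visits. The one practical consequence is that this question has to wait until the 1-year visits are complete.

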# 6. METHODS

## Study parameters and endpoints

Hypothesis

The hypothesis is that the application of CryoSeal (CS) during total knee replacement surgery is beneficial for the patient with respect to a faster track and improved postoperative rehabilitation. The beneficial effect may be due to quicker rehabilitation, by pain reduction, better mobilisation and quality of life (especially short time).

Primary endpoints

- postoperative knee function in extension difference as compared with preoperative extension function with goniometric at 2 and 6 weeks (in relation to secondary endpoints)

Secondary endpoints

- Grade flexion and extension difference after surgery
- Drain use or not
- Postoperative Hb/Ht
- Number of transfusions after surgery (according to appendix 1)
- Pain score
- Complications
- Total hospital stay and duration of rehabilitation
- Illness perception IPQ-K score
- Function improvement score (KSS, Barthel Index score, KOOS etc. see flowchart)
- Hand grip strength (measured with (Jamar) hand dynamometer)
- Activity Monitor

Study parameters

- Demographic data; gender, birth date (age), weight, length (BMI)
- Medical History; underlying diseases and home medication (including use of antibiotics prophylaxis and NSAIDs)
- Laboratory analysis; haemoglobin, haematocrit and blood view, CRP and erythrocyte sedimentation rate
- Operation details; anaesthesia, start- and end time of surgery, surgeon, type and time point placing and opening of drain, use of heparin, information about application of CryoSeal (if applicable), knee function after implantation of the implants
- Clinical data; number of transfusions (red cells, platelets and plasma), complications, removing drain, amount collected in drain, medication (including use of antibiotics and NSAIDs), discharge date
- Pain (score) at 24h post operative, and at 8:00 h each day until discharge from hospital.
- Rehabilitation; knee function during the first postoperative days, Barthel Index score and standard knee function scores (see Table 1).

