After subsequent primary and secondary analysis of the effect of CryoSeal using the primary and secondary endpoints as presented in Protocol 4.1 of the total RCT dataset, according to intention to treat (ITT) and according to treatment (ATT), also pre-specified subgroup analyses of the putative effects on the primary and secondary endpoints (estimated odds ratio (OR) and 95% interval between both study-arms) of CryoSeal will be performed.

1. The following hypotheses will be tested using three for the variables stratified subgroups:

1. Catheter use and no catheter use
2. NSAID-users and no NSAID-users
3. Age > 70 and ≤ 70 years, or categorized in 3 equal sized samples of age (for example: <60, 60-70, >70)

The corresponding hypotheses are:

1. Catheter can disturb the CS-sealing process of the wound and therefore decrease the postoperative knee ROM and mobility effect of CS

2. NSAID-use are prescribed to reduce pain perception and as anti-coagulation medication, which decrease postoperative knee ROM and mobility effect of CS

3. Age is associated with increased co-morbidity resulting in reduced wound healing, which increase postoperative knee ROM and mobility effect of CS in patients > 60 years

2. Separated in the CryoSeal arm and in the non-CryoSeal patients the following 19 pre-specified subgroups will be selected for MVA to identify whether these factors are important or not in the CS-effect. Subsequently, using the total study cohort de following subgroups are analysed by dichotomic (or continuous) comparison (Y/N) between CryoSeal use or not:

Combined subgroups using 4 variables:

1. Catheter use and no catheter use
2. NSAID-users and no NSAID-users
3. Age > 70 and ≤ 70 years, or categorized in 3 equal sized samples of age (for example: <60, 60-70, >70)
4. Women and men

Single subgroups using each variable (or not):

1. Peroperative Hb ≤ 6 mmol/L and > 6 mmol/L
2. Transfused and non transfused patients
3. Prednison-users and no Prednison users
4. Cemented and no cemented protheses
5. “Bloedleegte” surgery and no “bloedleegte” surgery
6. If catheter use: Bellovac and no low-vac catheter use
7. If transfused: trigger of perioperative RBC use at Hb ≤ 6 mmol/L and > 6 mmol/L
8. If transfused: Age> 60 and age ≤ 60 with trigger of perioperative RBC use at Hb ≤ 6 mmol/L
9. Surgery time > 2 hr and < 2 hr

Stepwize variables:

1. When drain used: Wound salvage production or not (Y/N)
2. When salvage production, reinfusion or not

Continuous variable:

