1. Is there a difference in postoperative complications (LoS, bleeding, pain, body temp.( if applicable)) with **reinfused autologous wound drain salvage** and no reinfused drain fluid after wound catheter use,
2. Costs calculation (hospital stay) of **drain use (all, incl. no autologous reinfusion) vs no drainage**, low-vac vs Bellovac vs no drainage (only Bronovo uses Bellovac, n=73),
3. postoperative QoL outcomes and drain use (all, incl. no autologous reinfusion)

List of postoperative outcomes (after 6 wk and 1 jaar)
- VG
- Medication
- Hand power
- BMI
- Barthel
- Oxford Knee Score
- KOOS
- SF12
- IPQ-K
- EQ5D
- Knee Society Score

Postoperative outcomes at hospital stay
-Postop complications, such as infections (deep and superficial wound infection, lung and urinary track infections),

-ROM and pain scores

-Postoperative bleeding

-Total hospital stay
-After two weeks: ROM, complicaties, pijnscore, Barthel, EQ5D, Oxford Knee

-Transfusion use: RBC transfusions, indications, triggers or type transfusion products
-Surgery time

Leiden, 15 May 2013

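### The reinfusion question compares bleeding and length of stay with all drained patients who were not reinfused, although reinfusion can occur only after salvage production

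*Combined protocol and SAP*

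**What the plan says.** The addendum closes with observational, post-hoc questions on the trial dataset. Four concern drains or reinfusion together with bleeding or complications. The plan uses catheter and drain for the same device.

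- **Postoperative variables, item 1:** "Is there a difference in postoperative complications (LoS, bleeding, pain, body temp.( if applicable". The groups are patients with reinfused drain salvage "and no reinfused drain fluid after wound catheter use".
- **Perioperative variables, item 7:** "Is there a correlation between perioperative wound drain reinfusion vs no reinfusion (if applicable) and postoperative complications". Bleeding is not named.
- **Perioperative variables, item 6:** "wound catheter (incl. autologous reinfusion, if applicable) use vs no use and postoperative complications (bleeding, body temp".
- **Perioperative variables, item 9:** "Blood losses associated with type of catheter used".

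The subgroup list earlier in the addendum (Stepwize variables) first splits drained patients by whether salvage was produced. Only then does it split them again: "When salvage production, reinfusion or not". The observational questions do not repeat this conditioning.

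On measurement, the study parameters in protocol section 6 include "removing drain, amount collected in drain". The secondary endpoints there also include postoperative Hb/Ht and the number of transfusions. Bleeding is not defined anywhere; Appendix 2 defines infections only. The addendum foresees univariate and then multivariate analysis, but names no adjustment for drained volume or clinic in these questions.

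**The concern.** Blood must be shed and collected before it can be reinfused, so part of the bleeding precedes the exposure and helps to decide who is exposed. Item 1 then uses bleeding as an outcome, together with length of stay, which may follow from bleeding. Its comparison group is every drained patient without reinfusion, including those whose drain produced nothing to reinfuse.

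A difference could therefore appear with no effect of reinfusion at all. It could be reported as more bleeding or a longer stay after reinfusion. Item 7 makes the same contrast on complications in general, so the same selection applies to any complication related to blood loss.

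**Working it through.** The documents give no sample size, effect or volume for these questions, so there is no stated figure to reproduce. The check has two parts: the order of events, taken from the plan, and an illustration of size, for which every input is assumed.

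**1. Order of events.** The stepwise subgroups run drain, then salvage produced or not, then reinfused or not. Item 1 runs drain, then reinfused or not. The middle step is missing, so drained patients without salvage fall into the comparison group.

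**2. Size under a simple model.** Let collected volume be standard normal, let half of the drained patients be reinfused, and let the decision correlate r with volume. With no reinfusion effect, the gap in volume is r × 2 × 0.798 SD.

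| r | Gap (SD) |
|---|---|
| 1 | 1.60 |
| 0.5 | 0.80 |
| 0.3 | 0.48 |
| 0 | 0 |

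The value at r = 1 is a ceiling. The value at r = 0 describes a decision unrelated to volume.

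**3. Size when volume decides.** Simulation of 1,000,000 patients per scenario. Assumptions: blood loss lognormal with mean 500 mL and CV 0.4 to 0.8; the drain collects 50% or 80% of it on average; reinfusion whenever the collected volume reaches 100, 200 or 300 mL; no reinfusion effect. These volumes illustrate the bias and are not proposed as clinical rules.

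- Reinfused patients show 253 to 645 mL more true blood loss, or 1.05 to 1.82 SD. The 1.82 comes from a scenario in which almost everyone is reinfused.
- On a marker not taken from the drain (assumed correlation 0.5 with blood loss), they still differ by 0.52 to 0.89 SD.

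**4. Size when volume decides only eligibility.** CV 0.6 (SD 0.6 × 500 = 300 mL), 80% collected, 200 mL needed, reinfusion at random among eligible patients:

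| Eligible patients reinfused | Difference, all drained | In SD | Top-decile bleeding, reinfused vs not | Odds ratio | Difference, eligible only |
|---|---|---|---|---|---|
| 30% | 85 mL | 85/300 = 0.28 | 12.2% vs 9.3% | 1.35 | 1 mL |
| 50% | 108 mL | 108/300 = 0.36 | 12.1% vs 8.5% | 1.48 | -1 mL |
| 80% | 187 mL | 187/300 = 0.62 | 12.1% vs 5.8% | 2.23 | 1 mL |
| 100% | 363 mL | 363/300 = 1.21 | 12.1% vs 0% | not finite | no comparison group |

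Here the whole spurious difference comes from patients who could not have been reinfused, and restriction removes it. If the decision among eligible patients also depends on volume, restriction alone is not enough. That is why adjustment for drain amount is needed as well.

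**5. Drain versus no drain (item 6).** If bleeding were read as drain volume, undrained patients would score zero and the difference would equal the mean drain volume, about 0.8 × 500 = 400 mL in this example. If it is read from Hb/Ht or transfusions, the measurement builds in no difference.

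**The case against.** A reader might infer something stronger: that the drain is itself the measure of bleeding, so that all the drain and reinfusion questions are circular and a difference is certain. The documents do not support that.

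- Bleeding is undefined and is listed among complications, so it may mean a clinical event. Postoperative Hb/Ht and transfusions are secondary endpoints that do not need a drain. For item 6 the circularity is therefore conditional.
- Item 9 can be a plain description of how much each drain type yields, a quantity that exists for every drained patient. Item 7 does not name bleeding. Items 2 and 3 under Postoperative variables, on costs and quality of life, do not use it.
- The stepwise list gives no volume threshold and does not say that volume drives the decision once salvage exists. Reinfusion may follow site or device. Section 3 ties drain use to clinical site, and the addendum states that one site alone uses Bellovac (n=73). Confounding by site may then be the main problem.
- The questions are labelled post-hoc and observational and ask about differences, correlations and associations. A causal report would be the reader's step.

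All of this stands and narrows the point. It does not remove it for item 1, whose comparison group is not limited to patients with salvage and for which no adjustment for volume is named. Pointing to Hb/Ht does not help there. The illustration shows a gap on an independent marker too, and reinfusion returns red cells, so the exposure itself alters Hb.

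**Conclusion.** The point holds for the reinfusion contrast, in conditional form. To the extent that reinfusion depends on the volume shed, item 1 is confounded by bleeding that preceded the exposure, and length of stay may inherit the bias. The order of events comes from the plan itself; how strongly volume drives reinfusion is not documented.

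The size is therefore a range: zero if reinfusion is unrelated to volume, 85 to 187 mL (0.28 to 0.62 SD) where volume decides only eligibility and 30% to 80% of eligible patients are reinfused, and above 1 SD where volume decides everything. All inputs behind these figures are assumed.

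For item 6 the defect is only the missing definition of bleeding. Item 9 may stand as description. Severity is low, because the randomised CryoSeal comparison is not affected.

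**What to change.** Amend the addendum as follows.

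- **Postoperative item 1, and the same contrast in perioperative item 7:** limit the comparison to drained patients with salvage production, as the stepwise subgroups already do. Drop bleeding as an outcome of reinfusion. Adjust the remaining outcomes for the recorded drain amount and, where reinfusion varies within clinic, for clinic.
- **Perioperative item 6:** take bleeding from measures recorded in all patients (postoperative Hb/Ht, transfusions), not from drain volume. Because this item counts reinfusion as part of drain use, note that returned red cells can affect Hb in that group.
- **Perioperative item 9:** keep it as a description of collected volume by drain type, stating that type is tied to site.

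The cost is wording and a smaller comparison set. Little or no contrast may remain if reinfusion follows site policy or if nearly all patients with salvage are reinfused; the item should then be reported descriptively. The protocol lists the amount collected without saying whether it was measured before reinfusion, so the adjustment may be imperfect and the report should say so.
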